### Secondary endpoints

The secondary endpoints are:
Need for new ventilation (invasive or noninvasive) 48 h after the arrest of initial ventilation, during a 21-day postoperative period.Renal failure occurring during a 21-day postoperative period according to the RIFLE classificationCardiac morbidity: daily serum troponin > 1.5 normal level (specific in each center) within the 48-h postoperative period.Cellular and tissue visceral impairment: daily serum D-lactate during the first 8-day postoperative period.Mortality at 60 days

This study is randomized in two arms on the day of surgery by drawing lots
Arm 1: patients with aortic clamping with preconditioningArm 2: patients with aortic clamping without preconditioning

### Eligibility

#### Inclusion criteria

Patients of at least 18 yearsSigned written informed consentPatients with thoracoabdominal aortic aneurysms (TAAA), type 1 to 5 according to Crawford/Safi classification, scheduled for open surgeryPatients with AAA requiring supra-visceral aortic cross clamping and reconstruction of the visceral arteriesPatients with TAAA with or without distal femoral perfusion assistancePatients with degenerative TAAA or post aortic dissection TAAAPatients having read and understood the information letter and signed the Informed Consent FormPatients affiliated to, or beneficiary of a social security coverage.

#### Exclusion criteria

Patients with AAA which require supra-visceral aortic cross clamping but not reconstruction of the visceral arteries (supra-visceral aortic cross clamping for juxta renal aortic aneurysms)Patients with TAAA which require a circulatory arrest (aortic aneurysms which affect all the descendant thoracic aorta and the aortic arch)Patients requiring emergency surgeryPatients receiving treatments that may interact with preconditioning such as nicorandil or oral antidiabetics.Pregnant women. Women who are not postmenopausal (≥ 12 months of non-therapy-induced amenorrhea) or not surgically sterile must have a negative serum pregnancy test within 1 week prior to randomization.Participation in another interventional clinical trial within 28 days prior to randomization and during the studyPerson deprived of liberty by administrative or judicial decision or placed under judicial protection (guardianship or supervision).

### Trial intervention

#### Surgical procedure

Surgical procedures were harmonized between the different centers during a common previous meeting after the protocol edition. The procedure for aortic surgical repair is well established and applied similarly in the different surgical centers. Cerebrospinal fluid drainage will be performed and monitored the operation and for the subsequent 48 to 72 h. Left heart bypass will be used: arterial cannulation will be carried out through the femoral artery and venous cannulation will be placed in the right atrium through the femoral vein. Distal bypass flows will be in range of 1.5 to 2 l/mn. Operation will be conducted with permissive hypothermia. Repair of the aorta will be driven through the sequential aortic clamping technique. When preoperatively identified, intercostal vessels destined for the spinal cord will be reattached to the aortic graft. Otherwise, all patent intercostal arteries from T8 to T12 will be reattached in the main graft. When possible, visceral arteries and the right renal artery will be repaired in a single aortic patch reattached in the main graft. Most of the time, the left renal artery will be repaired separately. Because of the rationale of the study, testing the efficacy of preconditioning for protection against the deleterious effects of ischemia-reperfusion, visceral and renal vessels will not be perfused.

Type IV TAAA will be operated without cerebrospinal fluid drainage and without left heart bypass but according the clamp and go technique.

#### Experimental group

The experimental group consists of patients receiving open TAAA surgery with direct preconditioning by clamping of the supra-visceral aorta.

Randomization allocation will be given to the surgeon during the procedure after intravenous injection of heparin, or after starting femoral assistance. The IPC will be a supra-visceral thoracic aortic cross clamping of 5 min followed by an unclamping period of 5 min. It will be repeated twice before starting the thoracic aortic cross clamping needed to perform surgery. The level of aortic cross clamping for IPC will be that required for aortic repair whose technique has been described elsewhere [35].

Postoperative follow-up will be the same as for standard OSR for TAAA. The follow-up period will cover the duration of hospitalization or will end on the 61st postoperative day in the event of prolongation of hospitalization beyond 60 days.

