## Background

Mortality rate after OSR for TAA is estimated between 4 and 15% [1, 2]. Pulmonary and renal complications can reach up to 50% and more [3, 4]. Compared to OSR for infrarenal abdominal aortic aneurysm (AAA), TAA requires repair of the visceral arteries with a supravisceral aortic cross-clamping often greater than 30 min. Following OSR for TAA, Serious lung damage reached 60% in large series [3, 5] and 40 to 50% in recent publications [6]. The hypothesis of a causal link between visceral ischemia and the occurrence of organ failure and particularly lung damage is the main focus of this study. Mesenteric ischemia reperfusion caused by aortic cross clamping above the celiac trunk and the superior mesenteric artery is involved in the onset of a systemic inflammatory response (SIRS) leading to multiple organ failure (MOF) [7–10]. Interestingly, distal perfusion of the aorta by a shunt reduces the onset of paraplegia, but increases the production of cytokines and complications associated with the inflammatory response [11, 12].

The main actors of the inflammatory response to ischemia-reperfusion are free radicals’ oxygen, polymorphonuclear neutrophil cells (PMN) and cytokines, all at the origin of the deleterious complications [13–15]. In particular, activity of neutrophils could be a key factor in remote lung injury [16, 17].

Beside remote lung injury, renal damage can be mainly attributed to direct effect of cross aortic clamping during TAA. Severe acute renal failure reaches 25% with dialysis required in 17% of patients [6] with an increased risk of death [18]. Wynn et al. reported that renal failure as defined in the RIFLE classification [19] was not associated with increased mortality [20]. According to Tshomba et al. [21] acute renal failure is often temporary. But even temporary, it is possible that acute renal failure observed in this context may later favour the onset of chronic renal failure [22].

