## Methods/design

### Trial objective

The primary objective of the study is to evaluate the efficacy of IPC applied directly to the supravisceral aorta during OSR for TAA with respect to acute kidney injury (AKI) according to KDIGO and pneumonia/prolonged ventilation-time during the 8-day postoperative period.

The secondary objectives are to compare both arms with respect to cardiac complications within 48 h, renal and pulmonary complications within 21 days and mortality at 60 days.

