#### Control group

Patients will receive standard OSR for TAAA without preconditioning.

Postoperative follow-up will be the same as for the experimental group.

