## Discussion

This project is original since no study has tested PCI as protective against lung and renal damages following OSR for TAAA.

Our hypothesis is that ischemic preconditioning may modulate the inflammatory response associated with visceral ischemia reperfusion caused by the cross clamping of the supra-visceral aorta and thus decrease clinical morbidity, and particularly lung damage. A direct individual benefit is expected with a decrease in mortality and a significant reduction in the total duration of hospitalization and in particular of the days spent in intensive care.

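### The follow-up rule ends at hospital discharge, which does not deliver the 60-day mortality endpoint; the two must be reconciled

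*Protocol article*

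**What the plan says.** The Trial objective section lists, among the secondary objectives, "renal and pulmonary complications within 21 days and mortality at 60 days", and the abstract says the same. The Secondary endpoints section repeats it as "Mortality at 60 days".

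The end of each patient's follow-up is set under Experimental group: "The follow-up period will cover the duration of hospitalization or will end on the 61st postoperative day". The same sentence limits the day-61 end to patients whose stay exceeds 60 days. The Control group section adds: "Postoperative follow-up will be the same as for the experimental group".

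The Follow-up section refers to Tables 1 and 2. Table 2 records death among the postoperative data, beside intensive care and hospital stay, without a day-60 time point or a post-discharge contact. The Study schedule gives 36 months of enrolment, 2 months of follow-up and 38 months in total.

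The Discussion expects a decrease in mortality and "a significant reduction in the total duration of hospitalization and in particular of the days spent in intensive care".

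**The concern.** Mortality at a fixed day needs each patient's vital status on that day. The rule under Experimental group stops observation at discharge and uses day 61 only to cap long stays. A patient who goes home on day 20 leaves follow-up on day 20, and a death on day 40 would not be recorded under that rule.

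Two things are at stake. First, the quantity measured changes from 60-day mortality to death in hospital up to about day 60. Second, the length of observation then depends on the length of stay, which the trial itself hopes IPC will change. If it does, the arm with the shorter stay has less time in which a death can be recorded. The study is open, so discharge may also be decided by staff who know the allocation. This is the only mortality endpoint, and vital status that was never collected cannot be restored in the analysis.

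**Working it through.** The plan states no figure on this point, so there is none to reproduce. The check sets the rules side by side and then illustrates the possible direction of bias.

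**1. What is known at day 60 under the written rule**

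| Patient's course | End of follow-up (Experimental group section) | Day-60 status |
|---|---|---|
| Dies in hospital by day 60 | Death | Known |
| Still in hospital beyond day 60 | Day 61 | Known |
| Discharged alive before day 60 | Discharge | Unknown |

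The third row is the gap. It applies to both arms, because the Control group section adopts the same follow-up.

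**2. Does another section close the gap?** Table 2 does not, since it names no contact after discharge. The 2-month follow-up in the Study schedule has two readings:
- It is the longest follow-up that the day-61 cap allows, with 36 + 2 = 38 months for the whole study. The gap then stands.
- It means 2 months for every patient. It then contradicts the Experimental group section.

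Either way the text has to be reconciled.

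**3. Possible effect on the comparison.** Let m be the true 60-day mortality, equal in both arms, and let c and t be the shares of 60-day deaths that fall after discharge, and so are missed, in the control and IPC arms. Recorded mortality is m(1 − c) in controls and m(1 − t) with IPC. The apparent risk ratio is (1 − t)/(1 − c), and m cancels. The shares below are assumptions, not figures from the document.

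| c | t | Apparent risk ratio, IPC to control |
|---|---|---|
| 10% | 20% | 0.80/0.90 = 0.89 |
| 20% | 40% | 0.60/0.80 = 0.75 |
| 10% | 40% | 0.60/0.90 = 0.67 |
| 20% | 20% | 0.80/0.80 = 1.00 |

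The last row matters as much as the others. If the missed shares are equal, deaths are under-counted but the ratio is not shifted.

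**4. Can the number of missed deaths be derived?** The Background says: "Mortality rate after OSR for TAA is estimated between 4 and 15"%. It gives no time horizon. Multiplying gives 110 × 0.04 = 4.4 to 110 × 0.15 = 16.5 deaths, but these are 60-day deaths only if the range is a 60-day figure. If it is an in-hospital rate, post-discharge deaths would come on top of it and not out of it. The only other mortality figure, about 1% before day 8 in the selected centres, says nothing about deaths after discharge. The share of deaths after discharge is not given. No count follows from the document.

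**The case against.** The strongest reply is that the trial probably does intend to follow everyone for 2 months. The Study schedule says 2 months, and the abstract, the objectives and the endpoint list all name day 60. This is also a journal article: the flow chart and some passages were not available for this review, and how a discharged patient is contacted is a detail usually left to the full protocol. That much stands. A reader might infer that 60-day mortality cannot be ascertained at all, and the text does not support that: deaths in hospital are captured, and a day-60 check may exist elsewhere. The reply does not remove the conflict, however. The article does not merely omit a detail; it states when follow-up ends, and that rule does not fit the endpoint.

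A second reply is that both arms share one rule, so no bias need arise. This stands in part. A reader might infer that the comparison is biased in favour of IPC, but that depends on IPC actually shortening the stay, which is a hope in the Discussion and not a design parameter.

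A third reply concerns size. A reader might take 20–30% of 4.4 to 16.5 deaths and conclude that about 1 to 5 would be missed (4.4 × 0.20 = 0.9; 16.5 × 0.30 = 5.0). The document supports neither the share nor the time horizon that this needs. The endpoint is also unpowered: with 55 per arm, 8 against 8 deaths becoming 8 against 6 gives a Fisher exact p of 0.78. Power to detect a halving from 15% is about 14%. The comparison is therefore largely descriptive, which lowers the urgency, but a descriptive mortality figure should still describe the quantity it is named for.

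**Conclusion.** The point holds as an inconsistency between a stated follow-up rule and a stated endpoint, and this part needs no assumption. Followed literally, the rule yields in-hospital mortality up to about day 60.

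The possible tilt towards IPC is conditional: it requires a shorter stay with IPC and, as a result, a larger share of its deaths after discharge. Under the assumed shares with unequal loss, the apparent risk ratio runs from 0.89 to 0.67 when the true ratio is 1. These figures show direction and plausible scale; they are not an estimate for this trial.

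Severity is should-fix. Mortality is one of five secondary endpoints, and neither the 8-day primary endpoint nor the sample size depends on day-60 status.

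**What to change.** Reconcile the Experimental group section with the Secondary endpoints and Study schedule sections. Suggested wording: vital status at postoperative day 60 is recorded for every randomised patient regardless of the date of discharge, by visit, telephone or hospital or civil records. Add the day-60 item to Table 2. Analyse 60-day mortality in all randomised patients.

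If a day-60 check is already in the full protocol, correcting the follow-up sentence is enough.

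The cost is one contact or record check for each patient discharged before day 60, at most 110, within the 2 months already scheduled. It changes data collection only, not care.

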#### Control group

Patients will receive standard OSR for TAAA without preconditioning.

Postoperative follow-up will be the same as for the experimental group.

### Follow-up

The data collected during the intervention and during the postoperative period are presented in Tables 1 and 2.

**Table 1 Tab1:** Data collected during surgery

Peroperative data collected	
**Total duration of intervention (mn)**	
**Duration of aortic clamping (mn)**	
**Duration of visceral arteries clamping** **(celiac axis, mesenteric artery, renal arteries)**	
**Duration of distal aortic perfusion (femoral assistance) when used**	
**mL of blood returned by the cell-saver**	
**mL of blood products transfused**	
**Peroperative urine output**	
**Hemodynamic monitoring points (when available): CI / BP / CF** **• before aortic clamping** **• during aortic unclamping** **• after aortic unclamping at 1, 3 and 24 h**	

*CI* Cardiac Index, *BP* Blood Pressure, *CF* Cardiac Frequency

**Table 2 Tab2:** Data collected during the postoperative period

Postoperative data	
**Duration of invasive or noninvasive ventilation (hours)**	
**Data on ventilatory monitoring for definition of moderate or severe acute respiratory distress syndrome, according to the Berlin definition** [34] **• moderate: (100 mmHg < PaO2/FiO2** **<** **200 mmHg) avec PEEP** **>** **5 cm H2O** **• severe: (PaO2/FiO2** **<** **100 mmHg) avec PEEP** **>** **5 cm H2O**	
**Arterial blood samples: lactates and blood gas at H1, H3 and daily (D1 to D8)**	
**Venous blood samples: serum creatinine at H3 and daily from D1 to D8**	
**Venous blood samples: Troponin on D1, D2**	
**Hourly urine volume output**	
**Duration of hemodialysis, if any**	
**Length of stay in intensive care unit**	

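### The 21-day RIFLE renal endpoint has scheduled creatinine only to day 8; separately, the lactate endpoint and Table 2 name different analytes and specimens

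*Protocol article*

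**What the plan says.** The Trial objective section of the protocol article includes among the secondary objectives a comparison of the arms on "renal and pulmonary complications within 21 days and mortality at 60 days". The Secondary endpoints section makes the renal part specific: renal failure over 21 postoperative days, graded by RIFLE. It also sets a marker of visceral damage, "daily serum D-lactate during the first 8-day postoperative period".

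The Follow-up section states: "The data collected during the intervention and during the postoperative period are presented in Tables 1 and 2". Four rows of Table 2 bear on this point:

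- creatinine: "Venous blood samples: serum creatinine at H3 and daily from D1 to D8"
- urine: "Hourly urine volume output", with no end day
- dialysis: "Duration of hemodialysis, if any", with no end day
- lactate: "Arterial blood samples: lactates and blood gas at H1, H3 and daily (D1 to D8", taken from arterial blood with no isomer named

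The Experimental group section limits observation: "The follow-up period will cover the duration of hospitalization or will end on the 61st postoperative day", the latter applying when the stay runs past 60 days. The Control group section gives that arm the same postoperative follow-up. Trial design describes the study as open.

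**The concern.** The article prints both a 21-day window for the renal endpoint and a stop at D8 for the laboratory value on which much of the RIFLE grading depends. A site that follows Table 2 would have no planned creatinine for the later part of the window.

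After D8, a patient whose creatinine rises without dialysis is counted only if a clinician happens to order a test, the result reaches the case report form, and the patient is still in hospital. In an open trial the decision to test can be made by staff who know the allocation. The Discussion also expects preconditioning to shorten the hospital stay. If it does, patients in that arm would be observed for less of the 21 days, and late renal events could be under-counted there.

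The lactate question is smaller. The endpoint names one analyte and specimen, and the data table names another. A site working from the table alone might not request a D-lactate assay.

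**Working it through.** No stated figure has to be reproduced; the check sets endpoint windows against the data schedule.

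**Renal endpoint**

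| Item | Days covered | Source |
|---|---|---|
| RIFLE renal failure | to D21 | Secondary endpoints |
| Serum creatinine | H3, D1 to D8 | Table 2 |
| Urine output | hourly, end day not stated | Table 2 |
| Hemodialysis duration | end day not stated | Table 2 |
| Follow-up | hospital stay, at most to day 61 | Experimental group, Control group |

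1. Days in the window without scheduled creatinine: 21 − 8 = 13 (D9 to D21).
2. Share of the window: 13 / 21 = 0.619, or 62%.
3. What the other two rows add after D8. Hemodialysis identifies dialysed patients only. The Primary endpoint section counts the injury, failure and loss classes as renal complications, so milder grades matter to this trial, and dialysis data cannot separate them. Hourly urine output could grade some patients for as long as it is recorded, but the table does not say that recording continues to D21, and it cannot show an event defined by creatinine.
4. Discharge. A patient who leaves hospital between D9 and D20 has no stated renal assessment for the remaining days of the window. A patient still in hospital at D21 remains in follow-up, but without scheduled creatinine after D8.

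**Lactate endpoint**

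| Item | Analyte | Specimen | Days |
|---|---|---|---|
| Secondary endpoints | D-lactate | serum | daily, first 8 days |
| Table 2 | lactates, isomer not stated | arterial blood | H1, H3, D1 to D8 |

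Daily sampling covers the 8 days of the endpoint, so 8 − 8 = 0 days are missing. Only the analyte name and the specimen differ. The venous rows of Table 2 name creatinine and troponin and no D-lactate.

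**The case against.** The strongest reply is that this is a condensed article. The full protocol, laboratory manual and case report form may hold a fuller schedule, including capture of routine creatinine after D8 and the D-lactate assay. That lowers confidence about what sites will actually record. It does not remove the conflict, because the article does not simply stay silent: it states a 21-day endpoint and a D8 stop.

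Second, a reader might infer that the schedule cannot support the 21-day endpoint at all. The documents do not support that. Urine output and hemodialysis carry no end day, so dialysis after D8 could be recorded without any creatinine test. Follow-up runs through the whole stay, and Study schedule gives a follow-up period of two months. This part of the objection stands. What remains is partial ascertainment after D8 and none stated after discharge.

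Third, a reader might infer that D-lactate has no sample on any day, or that the trial would end up with a general perfusion marker in place of a gut-injury marker. Neither is shown. The sampling days match, and the plural term in Table 2 neither names nor excludes D-lactate. The Background itself cites work that used blood lactate to gauge mesenteric injury. The lactate point is a naming mismatch only.

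Fourth, both arms have the same stated follow-up, so bias between arms is a possibility and not a demonstrated effect. That is correct.

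**Conclusion.** The renal point holds. As written, the plan would under-ascertain creatinine-defined RIFLE events from D9 to D21, which is 13 of 21 days. The 62% is a share of calendar days. It should not be read as a share of events missed, because the article gives no timing of renal failure after D8 from which to derive one. Any difference between arms would depend on unequal testing or unequal length of stay, which the documents make possible but do not establish.

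The conclusion assumes that Table 2 is the full list of planned collection, as the Follow-up section presents it, and that RIFLE classes are assigned at least partly from creatinine. Only a secondary endpoint is affected; creatinine is scheduled daily through the 8 days of the primary endpoint. The change should be made because it is cheap and determines what the trial can say about late renal injury.

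The lactate mismatch is minor and needs only consistent wording.

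**What to change.** Renal endpoint, one of two options:

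- **Keep the 21-day window.** Add a Table 2 row and case report form field for every routine creatinine from D9 to D21 or discharge, and state that discharge before D21 ends observation for this endpoint. Because that end of observation could differ by arm, report observed time by arm; length of hospital stay is already collected. The cost is transcription of results that exist anyway. A new mandatory D21 sample after discharge would be an extra procedure and is not needed.
- **Match the endpoint to the data.** Redefine it as RIFLE class to D8 plus dialysis to D21, and give the hemodialysis row that end day. The cost is wording, plus loss of any claim about non-dialysed renal failure after D8.

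Under the first option, state also the last day on which urine output is recorded.

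Lactate: either name D-lactate and its specimen in Table 2, or rename the endpoint as arterial lactate at the times already listed. Renaming costs wording only; naming D-lactate requires sites to confirm that the assay is requested.

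If the full protocol already contains these provisions, correcting the table and the endpoint text is enough.
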